## Abstract

**Background:**

Population ageing presents increasing challenges for health systems. Identifying complex needs and planning individualized care through Comprehensive Geriatric Assessment (CGA), promoting intergenerational engagement and empowerment via Service-Learning, are key strategies to support healthy and active aging. The general aim of the study is to evaluate the impact of a Service-Learning program that brings undergraduate health students into contact with community-dwelling older adults, assessing its benefits for students’ professional development and for older adults’ knowledge regarding their health.

**Methods:**

Research protocol for Service-Learning program with a mixed methodology and experimental intervention design, involving undergraduate students from Nursing, Physiotherapy, Human Nutrition and Dietetics, Occupational Therapy and Psychology degrees, and older adults from the community over 60 years old. The intervention at the university, consisting of three sessions, will be based on CGA. Student data will be collected during the final session using the questionnaire developed and validated by León-Carrascosa et al. (2020) to evaluate Service-Learning in higher education. After the first and last session, an additional questionnaire will assess satisfaction and perceived competency development. Older participants will be assessed with VIG-Frail, Integrated Care of Older People (ICOPE) screening tool, EuroQol 5D-5L, Nursing Outcomes Classification and sociodemographic data. They will complete a post intervention questionnaire regarding their satisfaction, perceived health status, knowledge of healthy lifestyle habits, and awareness of community resources, whose items will be evaluated using a 5-point Likert scale. Data will be collected through the REDCap platform and analysed using SPSS. Qualitative data from focus groups will undergo thematic analysis.

**Discussion:**

This study seeks to enhance both education and community health by integrating Service-Learning into health sciences training aligned with the WHO ICOPE framework. It aims to assess students’ perceptions of their preparation in geriatric assessment and person-centred care, while supporting early frailty detection and promoting healthy ageing in the community. Overall, it contributes to preparing future professionals for population ageing.

**Trial registration:**

This study was registered in *Clinical Trials* with the registration number NCT06890325 on March 24, 2025. As the registration occurred after the enrolment of the first participant, the trial was retrospectively registered.

**Supplementary Information:**

The online version contains supplementary material available at 10.1186/s12877-026-07312-1.

## Background

Population aging is a current global challenge, driven by increased life expectancy and declining fertility rates. Between 2015 and 2050, the percentage of the world’s population over the age of 60 will nearly double [1], with a direct impact on healthcare systems. In Catalonia (Spain), a similar trend is observed, with a rising dependency rate among older adults, posing a challenge for healthcare and social policies [2–6]. In Osona, Central Catalonia region, the population tends to increase, with the most significant growth observed among older age groups, particularly those aged 65 and over, who represented 18.6% of the population in 2024. Projections suggest that this trend of population ageing will continue in upcoming years [7, 8]. In this context, a progressive decline in physical and cognitive functions of older adults will lead to a greater population risk of frailty. In the first decade of the 2000s, the concept of frailty began to emerge to describe individuals undergoing the aging process. Frailty is defined as the geriatric syndrome characterized by a reduced physiological capacity to respond to external stressors, which increases the individual’s risk of falls, functional decline, disability, dependence and institutionalization [9]. Its prevalence ranges between 10 and 15% among community individuals aged 65 and over in Europe [10]. It has been described that the early detection of frailty enables a comprehensive approach, allowing individuals to maintain autonomy and improve quality of life for as long as possible [11]. Frailty often precedes dependency, when older individuals require assistance with daily activities. In more advanced stages, disability may develop, limiting individuals’ ability to live independently and affecting their quality of life.

These age-related conditions place significant pressure on healthcare and social care systems. Hospitals and long-term care facilities are increasingly required to provide complex, continuous care, while social services must respond to the growing demand for home support, community-based programs, and caregiver assistance. Furthermore, the rising costs associated with managing chronic diseases and age-related decline highlight the urgent need for preventive strategies, integrated care models and policies that promote healthy ageing. This situation points out the need for a shift from a traditional model of care, focused primarily on health problems, to one centred on the preservation of functional ability defined as the health-related attributes that enable individuals to be and act with that they value [12]. To develop person-centred intervention plans, it is essential to conduct assessments that enable the early detection of frailty and the design of preventive strategies to promote healthy ageing. Comprehensive Geriatric Assessment (CGA) is the gold standard of evaluating older adults, serving as a multidisciplinary diagnostic process that assesses medical, functional, psychological, and social capacities to eventually determine frailty status and various geriatric syndromes [13]. The use of CGA as a preventive tool in community older adults has been explored for several decades. Early studies already demonstrated the potential of CGA-based interventions to preserve functional capacity and delay disability [14]. Building on this foundation, the World Health Organization (WHO) established in 2015 a framework for action on ageing and health that set a goal of promoting and maintaining individuals. Functional ability is composed of intrinsic capacity, the environment, and the interaction between the individual and their environment. Intrinsic capacity refers to the composite of all the physical and mental capacities of an individual and represents the set of resources a person can draw on throughout life. The goal of intrinsic capacity is to measure individual’s capacities, not their deficits [15].

These new concepts of functional ability and intrinsic capacity call for their promotion and optimization as a strategy to prevent or slow the decline of these capacities over time. In this line, the WHO, in 2017, published a multidisciplinary guideline for the Integrated Care for Older People (ICOPE), which includes five key domains to evaluate the intrinsic capacity: cognition (cognitive decline), locomotor capacity (limited mobility), vitality (undernutrition), vision (vision impairment), hearing (hearing loss) and psychological capacity (depressive symptoms). Although the ICOPE screening tool is not yet validated, it is gaining increasing relevance, especially since the WHO released its second version in 2025, which added three key factors in older people’s health: urinary incontinence, carer support, social care and support domains [16–18].

Aligned with this approach, the WHO also launched the Decade of Healthy Ageing (2021–2030) with the goal of reducing health inequalities and improving the lives of older people, their families, and communities [12]. Several authors have hypothesized that intrinsic capacity assessed by these tools, may help identify individuals at higher risk of developing frailty, functional decline, and adverse health outcomes. If confirmed, these tools could be integrated into clinical practice for community-dwelling older adults, encouraging greater involvement in the management of their own health and improving self-care [19, 20].

In the context of an ageing population and the increasing burden of frailty, dependency, and disability, ensuring the training of future health professionals becomes more critical than ever. Preparing students in health-related fields to understand the complexities of ageing, promote healthy lifestyles, provide person-centred and interdisciplinary care is essential to meet the growing needs of older adults. Equipping future professionals with knowledge, empathy, and practical skills ensures their capability of addressing both the medical and social aspects of ageing. Knowledge about aging and older adults among undergraduate health students remains insufficient, as various studies indicate that they often hold negative perceptions about this population [21, 22]. In addition, to conduct a proper assessment, the attitudes of healthcare professionals and future professionals must be considered. Age is a determinant of health and is connected to ageism. Although it is present systemically in healthcare, characterizing and understanding the complex factors influencing ageism can positively impact the lives and health outcomes of older adults [23]. Increasing this knowledge has been identified as an effective strategy to reduce these negative attitudes [24]. Moreover, early exposure to real-world settings and vulnerable populations can foster a stronger commitment to geriatric care, ultimately contributing to more resilient and responsive health and social systems. It has been observed that the earlier young students have contact with older adults, the better their attitude towards this group [25].

The Service-Learning methodology is used as a framework, as it is an innovative teaching strategy through which students learn by participating in an intervention aimed at addressing a real community need. Through Service-Learning, students offer meaningful contributions to the community by engaging in direct, hands-on interaction. Several studies in the literature describe Service-Learning experiences involving students and older adults, such as telecollaborative projects during the COVID-19 pandemic, intergenerational programs focused on dementia, fall prevention initiatives, and interprofessional interventions like music and memory. These experiences consistently highlight the benefits of intergenerational learning, professional development, and improved attitudes toward aging [26–34]. However, none of the reviewed studies explicitly incorporated a CGA as part of their Service-Learning activities. This project therefore represents a novel intersection between two well-established but rarely integrated frameworks: CGA as a clinical tool, and Service-Learning as a pedagogical methodology. Highlighting this unique contribution more explicitly could help clarify the originality and added value of the study. One study evaluating updates to CGA emphasizes that integrating CGA into the care of older adults is crucial. The study highlights the relevance and necessity of including specific and thorough training on how to perform a CGA in undergraduate medical and nursing education [35].

In the current context of population aging, the prevention and promotion of health among older adults are crucial for achieving autonomy and improving quality of life. Although ICOPE has already been tested and explored in other European countries, such as France and Andorra [19, 36, 37], only one study has been identified in Catalonia, Spain where such testing has been conducted [38]. Furthermore, the training of future professionals to care for older adults is essential in the actual context. Service-Learning represents an innovative educational approach that strengthens students’ academic, professional, and civic competencies while promoting social responsibility and community engagement. In this regard, universities can play a key role as community health assets, acting as facilitators of intergenerational learning and health promotion. By linking education with real community needs, this type of initiative contributes to addressing the challenges of population ageing and to fostering healthier, more inclusive societies.

## Research aims

The general objective of this study is to evaluate the impact of a Service-Learning program that brings undergraduate health students into contact with community-dwelling older adults, assessing its benefits for students’ professional development and for older adults’ knowledge regarding their health.

Based on this general objective, the study addresses several specific goals for both students and older adults that operationalize the evaluation of the programme’s impact.

### Students

Analyse undergraduate health students’ perceptions of their professional training through the Service-Learning methodology, focusing on three interrelated dimensions: the formative development as an educational goal, the learning process as a means, and the service component as a commitment to the community.Identify distinct student profiles based on their responses to the Service-Learning questionnaire through a cluster analysis, and to examine how these profiles differ according to sociodemographic variables: age, sex, and university degree.Describe the impact of the Service-Learning intervention on soft skills: communication, interdisciplinary teamwork, and critical thinking.Describe the impact of the Service-Learning intervention on specific competencies related to Comprehensive Geriatric Assessment and Intrinsic Capacity.Compare students’ satisfaction levels, competences, and soft skills across different sessions.

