##### Students

A validated questionnaire developed by León-Carrascosa et al. (2020) is used to evaluate the students’ perceptions of the Service‑Learning methodology in higher education. The questionnaire consists of 29 items distributed across three dimensions that reflect the core components of Service-Learning: the formative aspect as an educational goal, the learning process as a means, and the service component as a commitment to the community. Each item is rated on a Likert-type scale ranging from 1 (strongly disagree) to 5 (strongly agree). The instrument has demonstrated adequate psychometric properties in terms of validity and reliability and has been previously applied in university contexts related to health and social education. The questionnaire will be self-administered by the students at the end of the third session.

An additional questionnaire was specifically developed for this research to assess students’ perceived acquisition of knowledge and competencies related to health promotion, disease prevention, CGA, and Intrinsic Capacity. It also includes items addressing transversal skills such as critical thinking, and problem solving, as well as perceived integration of knowledge and overall satisfaction with the project. Items were formulated in neutral language to minimise response bias related to positively or negatively loaded wording. The questionnaire will be self-administered at the end of the first and last sessions. As each session focuses on a different learning domain, the two assessments correspond to distinct sets of competencies rather than repeated measures of the same construct. Detailed items can be found in the supplementary material.

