### Statistical analysis

Descriptive statistics will be calculated for all study variables. Continuous variables will be summarised as mean and standard deviation for normally distributed data, or median and interquartile range for non-normally distributed data. Categorical variables will be expressed as absolute and relative frequencies (n, %). Normality will be assessed using the Kolmogorov–Smirnov test and visual inspection of histograms and Q–Q plots.

Mean scores for each dimension will be computed, and potential differences between degree programmes will be analysed using one-way ANOVA or Kruskal–Wallis tests, depending on data distribution.

A cluster analysis will be conducted to identify distinct student profiles based on their responses to the 29-item Service-Learning questionnaire covering the three dimensions of training, learning, and service. The K-means method will be applied, as it allows grouping students according to the similarity of their response patterns. Different values of *k* will initially be explored to determine the most meaningful and interpretable number of clusters. The final solution will be selected based on the internal coherence of the clusters and the clarity of their conceptual interpretation.

Once the final clusters are obtained, each group will be characterised by examining the mean scores of the questionnaire items or dimensions. This will allow the identification of distinctive patterns of perception and applicability of the Service-Learning methodology within each profile.

To examine how these profiles differ according to sociodemographic variables, subsequent analyses will be performed. Differences in age across clusters will be evaluated using ANOVA or the Kruskal–Wallis test when assumptions of normality and homogeneity of variances are not met. Associations between clusters and categorical variables such as sex and university degree will be assessed using chi-square tests.

A significance level of *p* < 0.05 will be applied to all statistical tests.

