For the limitations, a risk management plan has been developed to address them. One anticipated challenge is participant recruitment, which may be mitigated through collaboration with key community organizations or by offering visits at user locations. Another potential limitation is the non-attendance of older adults on session days; this may be addressed by converting the session into a role-play, practical workshop, clinical case discussion, or report preparation. The absence of a control group may limit the evaluation of intervention effectiveness. On the other hand, the specific objectives of the assessment of students’ soft skills and older adults’ knowledge is based on self-perceived evaluations, which may limit the validity of the results. Additionally, no pre-post test will be administered, which could reduce the reliability of the findings. No imputation methods will be applied for missing data, only complete-case analysis will be performed, acknowledging that this approach may reduce the statistical power of the results. Lastly, logistical challenges may arise, such as managing space, scheduling, and ensuring multidisciplinary interaction among student groups.

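### The objective to compare students' competences across sessions cannot be answered, because the protocol says the two assessments measure different competencies

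*Protocol article*

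**What the plan says.** Under Research aims, Students, the protocol article lists five specific objectives. The third and fourth are to describe the effect of the programme on soft skills and on competencies in geriatric assessment and intrinsic capacity. The fifth is a comparison of "satisfaction levels, competences, and soft skills across different sessions".

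Under Data collection methods, Students, two instruments are described.

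- The validated 29-item Service-Learning questionnaire: "The questionnaire will be self-administered by the students at the end of the third session". It is given once.
- A questionnaire built for this study, covering perceived knowledge and competencies. "It also includes items addressing transversal skills such as critical thinking, and problem solving", together with integration of knowledge and overall satisfaction. Its timing: "The questionnaire will be self-administered at the end of the first and last sessions".

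The protocol explains that each session has its own learning domain, so that "the two assessments correspond to distinct sets of competencies rather than repeated measures of the same construct". It refers to supplementary material for the items. Among the limitations in the Discussion it states that "no pre-post test will be administered, which could reduce the reliability of the findings".

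**The concern.** The objective asks for a comparison between sessions. The measurement section says that the only data available for it, as far as competences go, come from item groups that differ from one session to the other. Both statements cannot stand for competences.

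At stake is how a difference would be read. The abstract presents the twice-given questionnaire as measuring satisfaction and how students see their competencies developing. The Research aims section says the specific goals put the evaluation of the programme's impact into operation. The Discussion expects gains in communication, critical thinking, problem solving and teamwork. Against that background, a higher mean at the last session would easily be reported as growth in competence, when it might only show that the last-session items are easier to endorse or concern a different task. The study has one arm, so no control group would reveal the artefact.

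**Working it through.** No arithmetic applies. The point depends on no sample size, significance level or effect size, and the plan gives no figure for this objective to reproduce. The check sets the statements side by side.

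**1. Which instrument could supply the comparison?** A between-session comparison needs measurements at two or more sessions.

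| Student instrument | When given | Usable between sessions? |
|---|---|---|
| 29-item Service-Learning questionnaire | End of third session only | No |
| Purpose-built questionnaire | End of first and of last session | Only where the content is the same |

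The objective therefore rests entirely on the purpose-built questionnaire.

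**2. What does that questionnaire measure at each session?** By the protocol's own account, different competencies at the two sessions. The tasks differ too: students assess the older adult in the first session and present the report in the last.

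**3. What would the difference estimate?** Let A be the competence items of the first session and B those of the last. Write each session's mean as the level of the construct measured plus an item effect (how easily the items are endorsed):

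- first-session mean = level(A, first) + item effect(A)
- last-session mean = level(B, last) + item effect(B)
- difference = [level(B, last) − level(A, first)] + [item effect(B) − item effect(A)]

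If A and B are the same items, and students use them in the same way at both sessions, the second bracket is zero and the first is a change in one construct. If A and B differ, the second bracket is unknown and the first is not a change in anything, because it subtracts the level of one construct from that of another. More students shrink the standard error of the difference but leave both problems as they are. Pairing within student does not remove them either.

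**4. Does any other part reconcile the two statements?**

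- Statistical analysis describes comparisons between degree programmes and between clusters, and baseline associations among the older adults' instruments. Nothing there limits the between-session objective to common items.
- The limitation about the absent pre-post test agrees with the measurement section but leaves the objective in place.

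**5. How far does this reach?** The statement about different item groups concerns competencies. Transversal skills and satisfaction are mentioned separately. Whether their wording is the same at both sessions can be settled only from the supplement. The protocol makes no explicit exception for them, but it does not say that they differ.

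**The case against.** The strongest reply is that the objective says compare, and does not speak of change or improvement. Asking how students rated an assessment session against a report-delivery session is a coherent descriptive question, certainly for satisfaction. The authors also disclaim repeated measures and disclose that there is no pre-post test, so they themselves warn against reading the difference as change. Finally, this is the last of five student objectives. The study aim stated under Methods is students' perceptions on the three Service-Learning dimensions, measured with the validated questionnaire, and that is untouched.

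Much of this stands. It narrows the point and lowers its weight. It does not rescue the comparison for competences: setting scores on one group of competencies against scores on another has no clear meaning even as description, and the disclaimer in the measurement section is what contradicts the objective.

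A reader might go further in three ways that the document does not support.

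- *Every between-session difference is confounded with item content.* This is not shown for satisfaction or transversal skills, whose wording is not available here.
- *The plan lacks a paired analysis.* The article condenses a fuller plan, and a test for this objective may be specified there. No choice of test would repair the competence comparison in any case.
- *A false significant result is likely.* That would need the size of the item-content difference, the spread of scores, the within-student correlation and the number of students, none of which is given. The 304 under Power calculation is a starting reference for participants, taken from the social sciences and still to be adjusted; it is not a target number of students.

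**Conclusion.** The concern holds for competences. The objective to compare them across sessions contradicts the description of the only instrument given twice, and cannot be answered as written. For satisfaction and soft skills it is conditional: the comparison is sound in principle where an item is worded identically at both sessions, and fails for the same reason where it is not.

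The extent is one of three components of one of five student objectives. The Service-Learning dimension scores, the cluster analysis and the older-adult objectives are unaffected. The third and fourth objectives remain answerable as description. The conclusion assumes only that the protocol's statement about different competencies is accurate. If the supplement showed some competence items repeated word for word, that statement would need correcting, and those items could be compared.

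**What to change.** Three edits to the text:

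1. In the fifth student objective, delete competences from the list of things compared. Report the session-specific competence items separately for each session, without a test of one session against the other.
2. State that the across-session comparison covers only items worded identically at the first and last sessions, and list them from the supplement. If there are none, reword the whole objective as a description by session.
3. Analyse those common items as paired within student, which requires that a student's two responses can be linked.

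The first measurement is taken at the end of the first session, after exposure to the programme has begun. A difference in the common items should therefore be described as a difference between sessions and not as a before-and-after effect of the programme.

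The cost is the rewording of one objective and one analysis statement, plus a check of the items in the supplement. The price is that no between-session inference on competences will be available. No redesign of the questionnaire forms is needed. That matters because enrolment had begun before the trial was registered, and changing items part-way could split the data.
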